**Figure 1 F1:**
[figure not shown]
Proposed model of the factors of the intention to vaccinate.

For the open-ended question in which parents will detail their reasons for not absolutely adhering to the official vaccination schedule in their country, we will perform a qualitative analysis. After a pre-analysis, we will categorize answers based on the main reasons provided (e.g., medical reasons, considering vaccination risky etc.), and report the frequencies for each of them.

We will also check, using ANOVA, if there are differences in dependent variable (i.e., intention to vaccinate) according to participants' gender, marital status, while also considering whether vaccination is mandatory in their country of residence.

To check if the sources of information parents use to make vaccine-related decisions affect their intention to vaccinate, we will use ANOVA and *post-hoc* analysis.

### Anticipated results

The samples of this study will consist of data obtained in eight separate countries. This presents both challenges and possibilities. As some of the factors underlying vaccine hesitancy are context-specific and vary across time and place (Dubé et al., 2014), research in multiple countries is needed to understand vaccine hesitancy more fully on a local level. By analyzing our samples separately, we expect the study to contribute to knowledge on locally relevant factors related to vaccine hesitancy. However, the samples are unlikely to be representative in their respective countries, which limits the reliability of out conclusions on local, but not so much on the general level. Special care will also be taken to make sure that we sample people from all parts of the vaccine-hesitancy spectrum; the call for participants will be posted in different interest groups online along with general population call.

Given the sensitive nature of the topic, it is possible for the participants who participate in the study to have stronger convictions toward vaccines in one way or another, which might further decrease the representativeness of the vaccine hesitancy continuum—we want to include parents with various degrees of their hesitancy and strength of their convictions in order to avoid bipolarization. To decrease the effect of the topic on the motivation to participate, all the communication (e.g., invites, instructions) will be neutral in terms of referencing to potential harms and benefits of vaccination as well as any moral judgements of the decision.

Due to the wide range of phenomena of the present study, we hypothesize to find the following factors to reinforce the intent to vaccinate one's child: trust toward authorities, perceived social and scientific consensus, availability of relevant information, along with previously identified demographic characteristics and open-minded thinking. At the same time, we expect to confirm that vaccine hesitancy, perceived freedom, choice overload, the use of informal sources and susceptibility outcome bias serve as reinforces of delaying or omitting mandatory childhood vaccination. All our hypothesized connections can be seen in Figure 1.

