##### Elaboration of potential outcomes

The Elaboration on Potential Outcomes (EPO, Nenkov et al., 2008) measure will be used to assess participants' tendencies to generate and evaluate possible positive and negative consequences of their behavior, and measure their attitudes toward risk-taking. The instrument consists of 13 items, which are divided into three subscales with high internal consistency: generation/evaluation (e.g., “I try to anticipate as many consequences of my actions as I can”; α = 0.88), positive outcome focus (e.g., “I keep a positive attitude that things always turn out all right.”; α = 0.87), and negative outcome focus (“I am often afraid that things might turn out badly”; α = 0.87). The measure was also found to have strong factor structure, high test-retest reliability and high predictive validity (construct of EPO is an important determinant of self-regulation).

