### Proposed analysis

We will use statistical software (Matlab, R) for data analysis. We will analyse samples from each country separately because the differences in terms of language, legal framework in relation to vaccines, demographical characteristics and representativeness make the comparability between the different samples, and thus, their conjugate analysis, difficult (Ember et al., 1998).

For each sample, a factor analysis will be conducted to reduce the number of factors and control for interrelatedness of the variables. Two clusters of variables will be included: demographics (age, education level, number of children, mean age of children), and vaccine-related decision constructs (scores on scales on vaccination, vaccine hesitancy, perceived freedom of the decision, choice overload, actively open-minded thinking, trust toward authorities, availability of relevant information, perceived scientific consensus on vaccination, subjective estimation of percentage of children vaccinated on the country, perceived social consensus on vaccination, risk taking, and elaboration of potential outcomes). We expect the factor structure of each sample to be similar. With the reduced number of factors, a multivariate linear regression analysis will be conducted and the predictive power will be tested. The aforementioned factors will serve as predictors, and the parental intention to vaccinate (“I plan to vaccinate my child in accordance to the official vaccination schedule of my country”) will serve as criterion. All variables mentioned will also be included in a multivariate analysis of variance to see if there are differences between them depending on the level of adherence (total adherence, not completely total adherence, no adherence at all) to the official vaccination schedule of their children. We will test the proposed model of mediation (Figure 1) using regression analysis and compare it to a more complicated model with involvement as an additional factor.

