## Study 2—outcome, not the decision maker, makes the choice

### Introduction

In order to further explore involvement as a factor, we will set up a second study. When people are making decisions about important issues (i.e., vaccine-related), the involvement in the decision and the aforementioned phenomenon of choice overload may be exacerbated. This is because ‘the costs associated with making the “wrong” choice, or even beliefs that “wrong” choices do indeed exist, are much more prominent, and substantial time and effort would be required for choosers to make truly informed comparisons among alternatives’ (Iyengar and Lepper, 2000). As the complexity of making choices rises, people tend to simplify their decision-making processes by relying on simple heuristics (Wright, 1975; Payne, 1982; Payne et al., 1988, 1993; Timmermans, 1993). To test whether involvement and choice overload moderate cognitive aspects of vaccination decision-making, we will use one of the empirically well-established cognitive biases as a litmus test, the outcome bias.

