#### Outcome bias

People make and evaluate their own and other people's decisions every day, but different timings of these two cognitive processes lead to differences in available information (Baron and Hershey, 1988). All possible outcomes of a decision are mutually exclusive. In the moment of making a decision, the winning outcome and following consequences could not have been known to the decision maker, but these two factors are what the evaluator is familiar with. The outcome of a decision, however, should not be taken into account when evaluating the decision, because this information is irrelevant to the quality of the decision. The systematic tendency to evaluate the quality of a decision based on the outcome is called outcome bias (Baron and Hershey, 1988). People tend to use their knowledge about the outcome in an aforementioned, not logically justified manner (Allison et al., 1996; Gino et al., 2010), and judge the discernment and competence of decision makers based on it (Berg-Cross, 1975; Baron and Hershey, 1988; Lipshitz, 1989; Gino et al., 2010). However, there is no evidence on the relationship between the outcome bias and vaccine hesitancy, or outcome bias' connectedness to the level of parental involvement in the decision.

In the second study, involvement will be decomposed into three aspects: the situation decision makers are deciding about, decision makers' role, or who is a protagonist (parents vs. non-parents), and finally, low and high involvement health situations. Because the importance of the decision is related to susceptibility to cognitive biases, we expect that higher involvement among parents, compared to non-parents, will lead to greater proneness to making biased evaluations in health, but not in non-health related dilemmas (experiment 1). In a similar manner, parents will be more susceptible to outcome bias in both high and low involvement situations than non-parents (experiment 2). However, we expect that in dilemmas where the parents are the protagonists, the outcome bias will be stronger in non-parents (experiment 3).The results will help to understand the specific role of parents in vaccine decisions and will also contribute to the research about the relationship between vaccine hesitancy and cognitive biases, which at the current state is often hypothesized about, but lacking in papers.

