#### Procedure

After successfully completing Study 1, the participants will be asked to take part in the experiment. The experiment will be conducted at the Faculty of Philosophy of University in Belgrade, in classrooms equipped with computers. The non-parent sample will be collected separately, from the available pool of participants from general population in database of partner institution. Participants will, again, have a self-generated personal code as their identification. Each subject will be provided with an introductory explanation for the following part of the study and given detailed instructions. Each participant will read a prolog (the situation), the decision the protagonist made and the outcome of the decision will be explicitly stated, and then participants will evaluate that decision. This process will be repeated twice. After finishing the second round, participants will be asked to give consent to store and use the data obtained in the current session, then they will be presented with a thank you note along with a reminder to visit the venue again in a week. They will also be asked to provide their e-mail address to enable us to send them a reminder, and, if they wish, a personal result, in comparison with both samples. After completing the task in the following week, participants will be asked to give consent again, presented with a thank you note, and the authors' email addresses if they have any inquiries regarding the experiment. Debriefing will be provided immediately, with the repeated emphasis that the situations described in the tasks are simulations and that they are not based on real data. The procedure was ethically approved by the Institutional Review Board of the Faculty of Philosophy at the University of Belgrade.

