### Proposed analysis

The aim of this study is to investigate the moderating role of involvement in susceptibility to outcome bias.

Like in study 1, different samples will be treated separately. We will be using R and Matlab to conduct our analysis.

There is a possibility that participants might remember their answer from the first session and adapt their answer in the second session accordingly. To control this, we will use a two-way ANOVA. We will test whether the order of presentation of the stimuli, particularly whether the positive or negative outcome presented first, has an influence on the answers obtained during the second session.

To test our hypotheses, we will use a bivariate analysis of variance with repeated measures. As measures of the outcome bias, the difference between mean evaluations of decisions with positive and negative outcomes will be used to form 2 new variables for each of the 3 experiments. These new variables will then be used in the analysis. We will verify the assumption of standard distribution by conducting a Kolmogorov-Smirnov Test. If we cannot assume standard distribution, we will use the Wilcoxon signed rank test instead of an ANOVA. Effect sizes for each pair of tasks will be presented as Cohen's D.

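### Study 1 expects to confirm an outcome-bias effect it does not measure, the Study 2 introduction promises a choice-overload test its design lacks, and no linked analysis is described that could address either

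*Protocol article*

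**What the plan says.** **Outcome bias.** The Study 1 section Anticipated results lists it among the factors the authors expect to confirm: "the use of informal sources and susceptibility outcome bias serve as reinforces of delaying or omitting mandatory childhood vaccination". The definition comes in Study 2, section Outcome bias: "The systematic tendency to evaluate the quality of a decision based on the outcome is called outcome bias". The operational form is in the Study 2 Proposed analysis: "the difference between mean evaluations of decisions with positive and negative outcomes will be used to form 2 new variables" for each experiment.

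**Choice overload.** The Study 2 Introduction explains why outcome bias was chosen as the test case: "To test whether involvement and choice overload moderate cognitive aspects of vaccination decision-making". A three-item choice-overload scale belongs to the Study 1 battery.

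**Motivation.** The section Outcome bias states that "there is no evidence on the relationship between the outcome bias and vaccine hesitancy", and says that the results will contribute to research on that relationship.

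**Identification.** In Study 1 the participant composes a code from the parents' initials and month of birth. Its stated use is to find the record if the participant later withdraws. In the Study 2 Procedure: "Participants will, again, have a self-generated personal code as their identification". The Study 2 parents are Study 1 participants; the non-parents are recruited separately.

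**The concern.** Each study states an expectation that depends on a variable collected only in the other, and no analysis is described that brings the two together. As described, the Study 1 models cannot show whether parents more prone to outcome bias are less willing to vaccinate, and the Study 2 models cannot show whether choice overload strengthens the bias. The planned contrast of parents with non-parents does not fill the gap, because a difference between those groups carries no information on hesitancy. The stated motivation for Study 2 would then stay unanswered, although Serbian parents who take part in both studies supply the data needed to examine it.

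**Working it through.** **1. Outcome bias against the Study 1 measures.** By the article's definition, a measure must elicit ratings of decisions under good and bad outcomes. The Study 1 sections from the sociodemographic list to the elaboration scale describe no such task. The variables for the factor analysis and regression are named one by one, ending with "perceived social consensus on vaccination, risk taking, and elaboration of potential outcomes"; outcome bias is not among them. The multivariate analysis of variance reuses the same variables. The analyses of variance use gender, marital status, mandatory vaccination and information sources.

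The nearest entry is the elaboration scale, which assesses "tendencies to generate and evaluate possible positive and negative consequences of their behavior". That is forethought about one's own actions, not the rating of a decision already made by its result. The article does not call it a measure of outcome bias.

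As supporting evidence only, the measures of stated length add up, in the order they are described, to 1 + 5 + 10 + 14 + 4 + 3 + 7 + 8 + 1 + 1 + 25 + 13 = 92 of the 115 items (hesitancy scale taken as 14 after one item moved to the trust scale). The other 23 or so have to cover demographics, sources, involvement, consensus, norms and knowledge.

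**2. Choice overload against the Study 2 design.** The factors are domain, involvement, protagonist, outcome and parenthood. The procedure consists of reading a situation and rating the decision. The aim given in the Study 2 Proposed analysis names involvement alone. No choice-overload factor, scale or test appears.

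**3. Outcome bias against hesitancy.** The Study 1 models contain hesitancy and intention but not outcome bias. The Study 2 models contain outcome bias but neither hesitancy nor intention. No joint model is described.

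**4. What a linked analysis could detect.** The point itself rests on no figure in the article. The one sample size that bears on it is the Study 1 minimum of 222 per country. It reproduces with a noncentral F test: f² = 0.15, 20 predictors, N − 21 error degrees of freedom and noncentrality 0.15 × 222 = 33.3 give power 0.951 at alpha 0.05. The alpha of 0.05 and the target power of 0.95 are inferred, not stated.

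For a correlation between the outcome-bias score and intention or the hesitancy score, by Fisher's z,

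power ≈ Φ(atanh(r)·√(n − 3) − 1.96), with assumed r = 0.2 and atanh(0.2) = 0.2027.

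| Parents with both records (assumed) | 0.2027·√(n − 3) | Power |
|---|---|---|
| 40 (two parent situations × 20 per group) | 1.23 | 23% |
| 100 (illustrative) | 2.00 | 51% |
| 222 (all minimum-sample parents attend) | 3.00 | 85% |

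The smallest correlation detectable with 80% power, tanh(2.80/√(n − 3)), is 0.43 at n = 40, 0.31 at n = 80, 0.22 at n = 160 and 0.19 at n = 222.

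**The case against.** **Linkage is probably possible.** A reader might infer that the two data sets are held under unrelated codes, so that both claims are beyond testing. The article does not say that. The Study 1 code is a fixed recipe which the same person would reproduce, a self-generated code is used again in Study 2, and the Study 2 parents come from Study 1. What is missing is a stated common code and a described joint analysis. This objection stands.

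**Choice overload is not part of the formal aim.** The promise sits in the introductory rationale; the stated aim, the three experimental hypotheses and the design do not mention it. That is correct and makes this half the lighter one. It is still an explicit statement of what the study will test.

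**Figure 1 and Appendix 1 were not available.** An outcome-bias task in the full battery cannot be excluded outright. It is unlikely, given how specifically the measures and analysis variables are listed.

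**A condensed article may leave cross-study analyses to a fuller plan.** That would excuse missing detail. It does not explain an expectation attached to Study 1 when the listed Study 1 variables omit the construct.

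**Conclusion.** The mismatch holds on the text shown. Study 1 expects to confirm an effect of outcome bias without a described measure of it. The Study 2 introduction promises a test of choice overload that its design, procedure and analysis do not contain. The gap between outcome bias and hesitancy, given as motivation, is not addressed by any described analysis.

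It would be too strong to conclude that the experiments are compromised. The contrasts on domain, involvement and protagonist need neither linkage nor choice overload.

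A linked analysis would be only a partial remedy. The other countries, analysed separately, would still have no outcome-bias measure. Non-parents are not described as taking the choice-overload scale and would have no score. The power range of 23% to 85% depends on the assumed correlation of 0.2 and on attendance; the upper end needs all 222 parents to have usable records from both studies. The point should be corrected because two stated claims go beyond the described data, and the correction is cheap.

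**What to change.** 1. State that the same self-generated code is used in Study 1 and in both Study 2 sessions, and that it will be used to join the records. Put matching wording in the consent texts before data collection.
2. Add one secondary analysis in Serbian parents who complete both studies: relate the Study 2 outcome-bias score to intention and to the hesitancy score, and Study 1 choice overload to the outcome-bias score. Report estimates with confidence intervals, since power may be low.
3. Restrict the outcome-bias expectation in the Study 1 Anticipated results to that analysis, and limit the choice-overload statement in the Study 2 Introduction to parents.
4. If linkage is not wanted, delete both claims.

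The cost is a few sentences in the protocol and consent texts and one extra analysis. The downside is that records become linkable across the two studies under a pseudonymous code, which participants should be told.

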## Study 2—outcome, not the decision maker, makes the choice

### Introduction

In order to further explore involvement as a factor, we will set up a second study. When people are making decisions about important issues (i.e., vaccine-related), the involvement in the decision and the aforementioned phenomenon of choice overload may be exacerbated. This is because ‘the costs associated with making the “wrong” choice, or even beliefs that “wrong” choices do indeed exist, are much more prominent, and substantial time and effort would be required for choosers to make truly informed comparisons among alternatives’ (Iyengar and Lepper, 2000). As the complexity of making choices rises, people tend to simplify their decision-making processes by relying on simple heuristics (Wright, 1975; Payne, 1982; Payne et al., 1988, 1993; Timmermans, 1993). To test whether involvement and choice overload moderate cognitive aspects of vaccination decision-making, we will use one of the empirically well-established cognitive biases as a litmus test, the outcome bias.

#### Outcome bias

People make and evaluate their own and other people's decisions every day, but different timings of these two cognitive processes lead to differences in available information (Baron and Hershey, 1988). All possible outcomes of a decision are mutually exclusive. In the moment of making a decision, the winning outcome and following consequences could not have been known to the decision maker, but these two factors are what the evaluator is familiar with. The outcome of a decision, however, should not be taken into account when evaluating the decision, because this information is irrelevant to the quality of the decision. The systematic tendency to evaluate the quality of a decision based on the outcome is called outcome bias (Baron and Hershey, 1988). People tend to use their knowledge about the outcome in an aforementioned, not logically justified manner (Allison et al., 1996; Gino et al., 2010), and judge the discernment and competence of decision makers based on it (Berg-Cross, 1975; Baron and Hershey, 1988; Lipshitz, 1989; Gino et al., 2010). However, there is no evidence on the relationship between the outcome bias and vaccine hesitancy, or outcome bias' connectedness to the level of parental involvement in the decision.

In the second study, involvement will be decomposed into three aspects: the situation decision makers are deciding about, decision makers' role, or who is a protagonist (parents vs. non-parents), and finally, low and high involvement health situations. Because the importance of the decision is related to susceptibility to cognitive biases, we expect that higher involvement among parents, compared to non-parents, will lead to greater proneness to making biased evaluations in health, but not in non-health related dilemmas (experiment 1). In a similar manner, parents will be more susceptible to outcome bias in both high and low involvement situations than non-parents (experiment 2). However, we expect that in dilemmas where the parents are the protagonists, the outcome bias will be stronger in non-parents (experiment 3).The results will help to understand the specific role of parents in vaccine decisions and will also contribute to the research about the relationship between vaccine hesitancy and cognitive biases, which at the current state is often hypothesized about, but lacking in papers.

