### Methods

#### Design, sample, and procedure

Participants will be parents or primary caregivers of children that are of the recommended age to receive vaccinations from their corresponding countries across Europe and Asia (i.e., Finland, Germany, Hong Kong, the Netherlands, Serbia, Slovenia, and Spain). Participants must be (a) over 18 years old, and (b) a parent or care taker of at least one child under the age of 12 years (Salmon et al., 2005; Jones et al., 2012).

The sample size will be a minimum of 222 participants per country, based on a power analysis for an effect size of 0.15, and 20 predictors in a linear multiple regression model. The final sample size will not have a difference greater than 10% between each country. To make sure that there aren't any significant differences between the sample sizes of the different countries, if the sample of any country exceeds 10% of the mean, some participants will be randomly discarded until the criterion is met.

The questionnaire is programmed in JavaScript and will be administered online. To take part in the study, participants will need an electronic device with access to internet. The link with an unbiased invitation letter will be posted on different social media platforms, forums and websites, targeting a wide range of parents from the entire vaccine-hesitancy spectrum. Once the link is opened, participants will first be given a brief introduction of the study. Participants will then read and sign an informed consent, which states they are able to halt and withdraw from the study at any moment without providing a reason, and that they agree for their anonymized data to be analyzed for future publications. Participants will be asked to compose a unique identification code (consisting of their parents' initials, and month of birth), which will be used to identify their data if they decide to withdraw their data after completing the study. After that, participants will be asked to provide their demographic information and complete a battery of vaccination- and decision-making-related questions, with a total of 115 items (the complete battery is in Appendix 1). Participants will be able to leave items unanswered. The study will take ~25 min to complete, but will vary depending on participants' speed of responding. This procedure was ethically approved by the Institutional Review Board of the Faculty of Philosophy at the University of Belgrade.

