### Methods

#### Sample

The second study will be conducted in Serbia. The sample will be comprised of parents and caregivers that participated in Study 1, and additionally an equal number of non-parents. Non-parents will be matched with parents who participated in Study 1 in terms of their age, gender and education. To estimate the sample size needed for the second study, special attention was paid to the minimization of Type II error. The analysis results of the test strength show that detecting a statistically significant outcome bias effect by a bivariate analysis of variance (at level *p* < 0.01) of the effect size of.7, as reported by Baron and Hershey (1988), for a sample of 20 subjects per experimental group amounts to 99.9%.

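### Experiment 1 of Study 2 predicts no parent effect in non-health dilemmas, but the stated significance tests cannot support that half of the hypothesis, and the parenthood-by-domain interaction is not named

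*Protocol article*

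**What the plan says.** All references are to the protocol article, Study 2.

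- **Hypothesis** (Introduction, Outcome bias): higher involvement among parents than non-parents "will lead to greater proneness to making biased evaluations in health, but not in non-health related dilemmas (experiment 1").
- **Design**: each experiment is mixed, with parents and non-parents as the two participant groups. In Experiment 1, domain (health or non-health) is crossed with outcome.
- **Test** (Proposed analysis): "To test our hypotheses, we will use a bivariate analysis of variance with repeated measures". The analysis variables are positive-minus-negative outcome scores, two per experiment, which in Experiment 1 means one for health and one for non-health. If normality fails, a Wilcoxon signed rank test replaces the ANOVA. Cohen's D is promised for each pair of tasks, which is the outcome contrast and not the parent contrast. The section also says that different samples are handled separately, as in Study 1.
- **Sample size** (Sample): power to detect the outcome bias effect ("at level *p* < 0.01", "of the effect size of.7") "for a sample of 20 subjects per experimental group amounts to 99.9" percent. The same section says: "The sample will be comprised of parents and caregivers that participated in Study 1, and additionally an equal number of non-parents". For Study 1 (Design, sample, and procedure): "The sample size will be a minimum of 222 participants per country".

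**The concern.** The Experiment 1 hypothesis has two parts: a parent effect in health, and none in non-health. A significance test can support the first. It cannot support the second, because failure to reject may only mean that the comparison was imprecise.

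The domain contrast matters to the argument of the study. If the gap appears only in health, involvement is a credible explanation. If it appears in both domains, parents may simply be more prone to outcome bias in general. The Joint discussion would treat results that agree with the hypotheses as proof that parents are a special group and as a basis for tailored interventions. With a small sample, a non-significant non-health comparison is likely even when a real gap exists, so imprecision would work in favour of the predicted pattern.

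**Working it through.** **Step 1: what the plan's power figure covers.** Inputs from the Sample section are effect size 0.7, level 0.01, 20 per experimental group and power 99.9%. The metric of the effect size, the sidedness and the meaning of experimental group are not given.

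- Within-subject F test with f = 0.7, N = 20, two measurements and an assumed correlation of 0.5: noncentrality = 0.7² × 20 × 2 / (1 − 0.5) = 39.2 on 1 and 19 df. Power is 0.9990, which reproduces the stated figure.
- Two-sample t test with d = 0.7 and 20 per group, two-sided 0.01: noncentrality = 0.7 × √(20/2) = 2.21 on 38 df. Power is 0.323.

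The 99.9% fits the outcome effect, as the text says. It does not carry over to a parent versus non-parent contrast of the same nominal size at 20 per group.

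**Step 2: miss rate for a non-health parent effect.** Assumptions that are not in the documents: a true difference of 0.5 SD on the non-health bias score and a two-sided test. The 0.01 level is the only one Study 2 states; 0.05 is shown for comparison. With n per group, the noncentrality is δ = 0.5 × √(n/2) on 2n − 2 df, and the miss rate is P(|T| < critical t).

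| n per group | δ | df | Miss rate at 0.01 | Miss rate at 0.05 |
|---|---|---|---|---|
| 20 | 1.58 | 38 | 85.6% | 66.2% |
| 40 | 2.24 | 78 | 65.1% | 40.2% |
| 80 | 3.16 | 158 | 29.0% | 11.8% |
| 222 | 5.27 | 442 | 0.4% | 0.05% |

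The assumed difference matters. At 0.3 SD, 222 per group would still miss 28% at 0.01 and 12% at 0.05.

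**Step 3: what an interval could show.** In SD units, the half-width of the 90% CI is t(0.95, 2n − 2) × √(2/n). This is 0.53 at 20 per group and 0.16 at 222. Against an illustrative margin of ±0.5 SD, 20 per group is essentially unable to place the interval inside the margin, since 0.53 exceeds 0.5. By the normal approximation, with a true difference of zero and one-sided 0.05, 80% power needs 2 × ((1.645 + 1.282)/0.5)² ≈ 69 per group. At 222 per group the power exceeds 99%.

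**Step 4: does the stated analysis secure the interaction?**

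- In favour: the design is mixed with two participant groups, and the stated aim is to study moderation.
- Against: the analysis section never names parenthood by domain. It says samples are treated separately, and since Study 2 takes place only in Serbia, this could be read as separating parents from non-parents. The fallback is a paired test with no between-group term.

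The interaction is therefore a plausible reading but not a fixed part of the plan. Even if it is tested, it asks whether the gap is larger in health, not whether the gap in non-health is absent.

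**The case against.** The best reply is that a mixed design with a stated aim of moderation implies a parenthood-by-domain ANOVA, whose interaction is the right test. The hypothesis is also worded as an expectation and not as a commitment to show equivalence, and margins and contrasts are often left to a fuller analysis plan. This carries weight. The article does not rule out the interaction, and the absence of a formal equivalence test is not a fault in itself. What remains is that the analysis section does say how the hypotheses will be tested, and nothing it names can support the no-difference half.

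A reader might infer two stronger points that the documents do not support.

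- **That 20 parents and 20 non-parents is the plan.** The figure of 20 appears only in a power statement about the outcome effect, for an undefined experimental group. The same section takes its sample from the Study 1 parents, which allows 222 or more per group. Full attendance is not assured either: Study 1 is online, whereas Study 2 needs two classroom sessions a week apart. The actual n is unknown.
- **That the plan builds in a high rate of false health-only conclusions.** With a 0.5-SD parent effect in both domains, correlation 0.5, 20 per group and 0.05, simulation gives health significant in 34% of trials, and health significant with non-health not significant in 15%. That is 15/34 = 44% of the health-positive trials. The figure requires separate tests by domain, which no section prescribes, and the correlation, the effect size and the level are all assumed. With equal effects in both domains, a two-sided 0.05 interaction test would favour the prediction in only about 2.5% of trials.

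**Conclusion.** The point holds in a limited form. The no-difference half of the Experiment 1 hypothesis has no stated analysis that could support it, and the interaction that would carry the domain claim is not named. This is true at any sample size. The practical size depends on n, which the article leaves open: for an assumed 0.5-SD difference at two-sided 0.01, the miss rate runs from about 86% (20 per group) through 65% (40) to under 0.5% (222). At 0.05 the corresponding figures are 66%, 40% and under 0.1%. Both the 0.5 SD and the 0.05 level are assumptions of this review. The point limits what Experiment 1 may conclude about domain specificity; it does not affect the test for outcome bias itself.

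**What to change.** 1. In the Study 2 Proposed analysis, state that the domain claim rests on the parenthood-by-domain interaction, in the predicted direction, in one model containing both participant groups, together with the parent versus non-parent difference in health. Clarify that treating samples separately does not mean analysing parents and non-parents apart, and that any non-parametric fallback keeps a between-group comparison.
2. Report the non-health parent minus non-parent difference with its confidence interval.
3. Claim that there is no effect in non-health dilemmas only if that interval lies inside a margin the investigators set in advance and justify. Otherwise report that part as inconclusive.
4. In the Sample section, define experimental group, and reconcile the 20 per group with the sample drawn from Study 1.

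The cost is a few sentences and one confidence interval, with no new data. The downside is that with a small sample the non-health part will probably be inconclusive: about 69 per group would be needed for 80% power under the illustrative ±0.5 SD margin.
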